#### Clinical baseline examination

During the initial clinical examination (Additional file 4) visit, the chiropractor will perform a thorough neurologic examination to identify findings requiring immediate medical attention or referral to a pediatrician connected to the project (Additional file 5). If none are found, the chiropractor examines the spine, pelvis and temporomandibular joints for biomechanical dysfunctions to assess whether the child is a candidate for chiropractic manipulation (Additional file 6) and if there are no exclusion criteria present, the child will be offered to enter the trial (see Table 1).

At this visit, all participants and their parents are informed about possible side effects known to chiropractic treatment and are told to keep track of all such effects in order to be able to report them to the chiropractor. They are also told that information about trauma experienced during the trial period will be noted at each visit as well. If the participant and his/her parents then consent to participate in the trial, the participant is randomized.

#### Randomization

Participating children are randomized with 1:1 allocation using random block size with the software nQuery Advisor [30] by the data manager at NIKKB upon receipt of the consent form. Group assignment is noted in opaque envelopes and sent to the project clinic.

When the child has completed the 4 weeks pre-treatment period and is found eligible for inclusion at the clinical examination visit, the randomization envelope from NIKKB will be opened by the primary investigator and the trial period of 4 months will begin. Neither the child nor the parents are informed about group allocation.

### Interventions

All participants from both groups receive oral and written advice about lifestyle beneficial to headache patients in general. Healthy habits that include regular sleep, exercise, fluids and meals are considered a cornerstone of treatment [21]. Therefore, we have designed a list of basic advices concerning lifestyle that we think are commonly known and generally accepted in the population. We have made these advices as simple and understandable as possible in order to make them easily applicable to the participants (Additional file 7).

The parents are then asked to leave the room, and participants in both groups are examined via static and motion palpation of the entire spine, pelvis and temporomandibular joints. After this examination, either the chiropractic manipulation or the sham manipulation is administered. Thus, each consultation resembles a normal consultation with a chiropractor in both groups.

#### Chiropractic manipulation

The children in the chiropractic manipulation treatment group receive chiropractic manipulation as indicated according to the examination utilizing a specific contact, high-velocity, low- amplitude, short lever technique with a thrust given according to the determined line of drive, resulting in an audible joint cavitation [31]. If treatment is indicated in the lumbar spine or the pelvis, the child will lie on the side as indicated by the clinical findings, with the upper knee bent and the chiropractor supporting the upper shoulder while stabilizing the patient’s leg and hip with her own leg and delivering a high-velocity, low-amplitude thrust. If manipulation of the thoracic spine is determined to be indicated, a high velocity, low-amplitude thrust will be given with the patient in a prone position. If treatment in the neck is indicated, the child will sit on a chair and the chiropractor will stand behind the patient while contacting the spinous process of the joint to be manipulated and a high velocity, low-amplitude thrust is given. All treatments are modified to fit the age and size of the child as well as individual joint characteristics.

To reflect daily clinical practice, this treatment is given pragmatically, i.e. the number and frequency of treatments, as well as the joints treated, are based on the chiropractor’s individual evaluation at each visit. Number and dates of treatment as well as joints treated will be noted.

#### Sham manipulation

The placebo treatment is very similar to the placebo treatment described by Chaibi et al. [32] utilizing the same treatment positions and patient placements as used in the chiropractic manipulation group. The sham manipulation consists of a broad, non-specific contact, low-velocity, low-amplitude gentle push in a non-intentional direction. All contacts are performed away from the spinal column without soft tissue pretension, so no joint cavitation occurs. The participant will first lie on the right side with the left knee bent where the chiropractor holds on to the participant’s left shoulder and the left gluteal region while delivering the light non-intentional push, equivalent to approximately half a pound of pressure, on the lower, lateral part of the gluteal muscle with no cavitation from the lumbar or sacroiliac joints. Afterwards the child will lie prone on the treatment table while the chiropractor places a hand on each of the participant’s lateral scapular edge and delivers a light push, equivalent to approximately half a pound of pressure, with no resulting joint cavitation. Finally the participant sits in a chair and the chiropractor puts a hand on the participant’s left trapezius muscle, puts a de-activated activator instrument [33] on the chiropractors own left forearm and ask the participant to turn the head to the right. At the moment when the participant turns the head, the chiropractor will give a click with the de-activated activator. This procedure will then be repeated on the other side, again with no cavitation of any joints. Each participant in this group is given a total of eight visits with sham manipulation with four visits during the first month of participation, two the second, one the third and one during the fourth attempting to resemble a common course of care in a chiropractic practice.

#### Blinding

Blinding of the participating chiropractor in this trial is obviously impossible. Blinding of the participants is attempted by not revealing the group allocation and by including a sham manipulation that closely resembles the active treatment. Furthermore, eight visits are given in the sham manipulation group to resemble the estimated number of treatments in the chiropractic manipulation treatment group to reduce attention bias. Also, in the control group an activator treatment [33] used on the chiropractor’s own arm in order to produce a noticeable clicking noise resembling a joint cavitation. Blinding of the parents is attempted by not inviting them to observe the treatment. At the end of the treatment period, participating children and their parents receive a question asking them, which of the two groups they believe they have been participating in.

At all sessions in both groups, parents are allowed to be present during the interview where the chiropractor will ask about headaches, side effects experienced after the previous treatment according to a checklist (Additional file 8), and the participant will also be asked if he/she has experienced any trauma since the last visit, and if so, the characteristics of the trauma.

### Collection of data

#### Baseline data

Baseline data will be collected prior to the pre-treatment period by a questionnaire including the following items:agesexduration and frequency of headache problem prior to inclusioncharacteristics of headache problemprior examinations and/or treatment of headachefamily history of headachetrauma to head and/or neck prior to inclusionneck and/or back painother health problemsdiet, sleep and exercise habitssportssocioeconomic statussmoking in the home

#### Outcome data

Throughout the study period, parents and participants answer the same weekly text messages on their mobile telephone as during the pre-treatment observation period, independent of the chiropractor.

At the end of the 4 months of treatment, all participating families receive a final text message including three questions:“How satisfied is <child’s name> with participation in this trial on a scale from 0-10, where 0 is the worst and 10 is the best you can imagine?”“How has the headache changed since <child’s name> started the treatment at the chiropractor? 1. almost gone/disappeared. 2. much better. 3. a little better. 4. same. 5. a little worse. 6. much worse. 7. worse than ever.”“In this trial there have been two groups. Do you think that <child’s name< was in group 1, who had standard chiropractic treatment or in group 2, that DID NOT have standard chiropractic treatment (please answer 1 or 2)?”

All participating families receive a questionnaire 1 year after entering the trial, including questions about headache status of the child as well as other treatments received for headache (Additional file 9).

#### Additional information collected during the trial period by the chiropractor

number of treatmentsarticulations treated (recorded at each visit)numbers, severity and character of traumas/accidents experienced between visits while participating in the trial (recorded at each visit)side effects experienced between two treatments (type, timing and duration; recorded at each visit)other diseases reported/identified during treatment periodnumber and reasons for drop-out

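### Side effects, a secondary outcome, are described as collected only by the unblinded treating chiropractor at the next visit, with no scheduled question after the last treatment

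*Protocol article*

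**What the plan says.** The Protocol article, *Secondary outcomes*, lists the character and duration of side effects. *Statistical analyses* says that secondary outcomes are analysed in the same way as the primary ones, so they are to be compared between arms.

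Collection is described in these places:

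- Under the heading "Additional information collected during the trial period by the chiropractor", the chiropractor records "side effects experienced between two treatments (type, timing and duration; recorded at each visit". The same list includes how many children drop out and why.
- *Blinding* says that at every session the chiropractor asks about "side effects experienced after the previous treatment according to a checklist (Additional file 8"). It adds: "At all sessions in both groups, parents are allowed to be present during the interview". It also says that this chiropractor cannot be blinded.
- *Clinical baseline examination* tells families to note side effects and report them to the chiropractor.
- *Outcome data*: the weekly text messages, collected independently of the chiropractor, cover headache days, intensity and pills. At the end of treatment "all participating families receive a final text message including three questions": satisfaction, change in headache and believed group. The one-year questionnaire is described as covering headache status and other treatments.

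On visit numbers, *Sham manipulation* states: "Each participant in this group is given a total of eight visits with sham manipulation". In the active arm, "the number and frequency of treatments, as well as the joints treated, are based on" the chiropractor's judgement at each visit. *Blinding* explains that eight sham visits were chosen to be similar to the number expected in the active arm.

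**The concern.** If treatment k is asked about at visit k+1, the last treatment has no visit at which to ask about it, and neither has the last treatment of a child who stops coming. Those who stop are a group in whom side effects matter.

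The interviewer also gives the treatment and knows the arm. The headache outcomes are protected from this by text messages that bypass the chiropractor; the side-effect outcome is not.

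Finally, the number of times a child is asked is fixed in one arm and decided by the unblinded chiropractor in the other. The authors present this as the first randomised trial of this treatment in children with recurrent headache, so its side-effect results will be relied on.

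**Working it through.** The plan gives no figure on this point to reproduce. The check is a comparison of the described channels, then a count.

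**Channels described**

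| Channel | Depends on chiropractor | Described as asking about side effects | Covers time after last treatment |
|---|---|---|---|
| Checklist at each visit | yes | yes | no |
| Family reports to chiropractor | yes | on the family's initiative | not scheduled |
| Drop-out reason | yes | only if it is the reason | reason only |
| Weekly text message | no | no | up to week 17 |
| Final text message | no | no | yes |
| One-year questionnaire | no | not mentioned (Additional file 9 not shown) | yes |

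No row combines independence from the chiropractor with a described side-effect question, and no row gives a scheduled side-effect question after the last treatment.

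**Share of treatments without a scheduled question**

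With k treatments, k − 1 intervals are asked about, and the share not asked about is 1/k.

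- Sham, k = 8 (stated): 7 asked about, 1/8 = 12.5% not.
- Active, k not stated. Assumed range 4 to 12: 1/4 = 25% to 1/12 = 8.3%. This also assumes that every active visit includes a treatment.

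**Effect of unequal visit numbers**

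Assume the same independent risk p = 0.10 per treatment in both arms. The chance of at least one recorded effect is 1 − (1 − p)^(k−1). With every treatment followed up it would be 1 − (1 − p)^k.

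| k | As recorded | Every treatment followed up |
|---|---|---|
| 4 | 1 − 0.9^3 = 27.1% | 1 − 0.9^4 = 34.4% |
| 8 | 1 − 0.9^7 = 52.2% | 1 − 0.9^8 = 57.0% |
| 12 | 1 − 0.9^11 = 68.6% | 1 − 0.9^12 = 71.8% |

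Gap between 8 and 4 treatments: 25.1 points as recorded, 22.6 with full follow-up. Gap between 12 and 8: 16.4 against 14.8. The missing last interval adds 2.5 and 1.6 points. The ratio of the full to the recorded gap is exactly 1 − p, here 90%; at p = 0.05 it is 95% and at p = 0.20 it is 80%. Most of the gap is exposure: more treatments give more side effects.

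The figures above contrast individual children. For an active arm split evenly between 4 and 12 visits, which averages the intended eight, the recorded share is (27.1 + 68.6)/2 = 47.9%, against 52.2% in the sham arm, a gap of 4.3 points. With full follow-up it is (34.4 + 71.8)/2 = 53.1% against 57.0%, a gap of 3.9 points.

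**The case against.** Three stronger readings are tempting, and the document supports none of them.

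- *That effects after the last treatment, or effects leading to drop-out, are never recorded.* Reasons for drop-out are on the chiropractor's list, and families are asked to report effects. The side-effect checklist and the one-year questionnaire (Additional files 8 and 9) are not shown. In the active arm, a closing visit without manipulation is not excluded. What stands is that no scheduled question after the last treatment is described. A drop-out reason also does not supply the character and duration that the outcome names.
- *That ascertainment differs between arms.* Both arms have the same interview at all sessions, and eight sham visits were chosen to match the expected active number. If the match holds, the average difference in opportunity largely disappears. A difference is possible, because one schedule is fixed and the other is not.
- *That a difference such as 52% against 27% would be spurious.* It would be about 90% exposure under the same assumptions. The proportion of children with any side effect is also not the outcome that the protocol names.

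On the unblinded interviewer, the other side can fairly say that a provider of manual treatment cannot be blinded, that the informants are the child and parents, whose blinding is attempted, that a checklist is used, and that parents may be present. These reduce the risk of biased recording. They do not remove it, since one person both asks and records.

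Timing also counts against the remedy. *Recruitment* reports 180 children included by January 2019, so a new item reaches a minority.

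**Conclusion.** The point holds as a modest weakness in how a secondary outcome is collected. As described, side effects come only through the unblinded treating chiropractor at return visits. The last treatment has no scheduled question: 1 in 8 (12.5%) in the sham arm, and 8.3% to 25% in the active arm if children there have 12 to 4 visits. No structured record is described for a child who does not return.

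Unequal numbers of treatments and recording occasions are a risk to report, not an established bias. The sham figure rests on the stated schedule. The active figures rest on assumed visit numbers, and the percentages of children with any effect rest also on an assumed, constant 10% risk per treatment. The headache outcomes are not affected.

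**What to change.** 1. Add one side-effect item (yes/no, then short type and duration) to the final text message. For children still in treatment or yet to enter, add it to the weekly message too. Both go to the data manager's system, not through the chiropractor, and reach a child who stops visiting but still replies.
2. Keep the visit checklist. Analyse it by arm as a rate per recorded treatment, allowing for repeated treatments within a child.
3. Report by arm the number of treatments given, the number of last treatments without a side-effect record, and the number of drop-outs without one.
4. Report the text-message data separately from the checklist data. A comparison of any side effect over the treatment period should stand beside the number of treatments, because exposure may differ.

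The cost is a short amendment, one item in an existing system and a slightly longer message for families. Coverage is partial. With 180 of the planned 240 included by January 2019, at most 240 − 180 = 60 further children, plus those still in treatment, could supply the new data; fewer if the amendment takes effect later. Items 2 and 3 need no new data collection. No treatment rule changes.

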### Variables

#### Primary outcomes

*For each week we will consider three variables based on the weekly SMS:*
Number of days with headache per weekHeadache intensity on a pain scale from 0 to 10 per weekNumber of headache pills per week

To catch the effect of the intervention, we will consider the average values during the pre-treatment period and the final 4 weeks of the study period (week 14–17). Three primary outcomes are then given by the change over time, i.e. the difference between the average values from the final 4 weeks and from the pre-treatment period. The primary outcomes are prioritized as listed above. A fourth primary outcome is the global perceived effect (GPE) after 4 months based on the final SMS.

#### Secondary outcomes

Character and duration of side effects experienced after treatmentHeadache status after 1 year (questionnaire)General perceived effect after 8 months for children reporting little effect, no effect or worsening of headache in the final SMS after the treatment period and subsequently received care from the pediatrician if they had received chiropractic manipulation, or a course of chiropractic manipulation if they had received sham manipulation

### Follow-up procedures after the treatment period

Children in the sham manipulation group reporting little effect, no effect or worsening of headache in the final SMS after the treatment period are offered free chiropractic care, similar to the care delivered in the manipulation group, during the trial for 4 months following the trial period. After the four-month post-trial treatment period, parents will receive a final text message, identical to the one they received after participating in the trial regarding the effect of the treatment. If they still report little effect, no effect or worsening after treatment, they will be offered a consultation with the trial pediatrician.

Children in the chiropractic treatment group reporting little, no effect or worsening after treatment will be offered a consultation with the pediatrician, and after 4 months they will receive a final text message, identical to the one they received after participating in the trial.

### Sample size considerations

Sample size depends on the expected change on the primary outcome as well as the average values of the outcome and the inter-individual variation. Because this is the first study using an assessment of these endpoints shared by parents and children in a child population aged from 7 to 14 years, we do not have any reliable information on the population means and variations in the intended primary outcomes. We hence decided to perform a sample size calculation when the data collection was completed for 50 children in each treatment group. We decided to use number of weekly headache days as basis for this calculation, since this is our initially highest prioritized primary outcome candidate. The mean number of weekly headache days during the 4 weeks pre-treatment was 11 days (2.75 days/week). The standard deviation of the change in number of weekly headache days from pre- to post treatment was 5.58 and normally distributed. Based on consensus among the authors, 20% of weekly headache days was decided to be a clinically relevant reduction, because it is close to half a day per week in relation to the mean pre-treatment weekly headache days. Thus, a sample size of 100 children in each group is needed to detect a difference of 20% of the pretreatment mean (0.55 day/week) with a power of 80% and a significance level of 5%. Calculations were performed in nQuery Advisor [30]. Allowing for a 20% drop-out rate, the aim for inclusion will be 240 children.

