**Methods:**

Children with weekly headaches for at least six months will be included if they have indications for chiropractic manipulation. The participants will be randomized to either chiropractic manipulation or sham manipulation. Both children and parents will be blinded for allocation. There will be 100 children in each arm and they will answer weekly text messages four weeks prior to treatment and during a four months treatment period. Potential primary outcomes are weekly number of headaches, intensity of headache, medication use and global perceived effect. Secondary outcomes include side-effects and headache status after one year.

An initial outcome data analysis will be performed to inform the choice of primary outcome (adaptive design). Intervention effects will be reported as the difference in mean values between the two treatment arms, Cohen’s effect size and numbers needed to treat.

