## Method

### Procedures

#### Recruitment

The recruitment for this trial began November 2015, by January 2nd 2019, 180 children were included and recruitment is expected to be concluded by June 2019. School principals in the region of Northern Jutland, Denmark, are contacted by telephone and asked for permission to distribute an invitation (Additional file 1) to all 1st -7th grade children through the Danish School Information Network, which is the official communication line between the school, the child and the parents. Furthermore, information is distributed through local newspapers, television and radio, as well as social media. Parents with children aged 7–14 suffering from recurrent headaches are invited to contact the project clinic for screening for inclusion in the trial.

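### The inclusion target of 240 does not retain the required 200 children at the stated 20% drop-out; it leaves 192, with about 78% power rather than 80%

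*Protocol article*

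**What the plan says.** In the protocol article, under Sample size considerations, the calculation rests on data from the first 50 children in each group. The inputs are "The mean number of weekly headache days during the 4 weeks pre-treatment was 11 days (2.75 days/week") and "The standard deviation of the change in number of weekly headache days from pre- to post treatment was 5.58 and normally distributed". The result is: "Thus, a sample size of 100 children in each group is needed to detect a difference of 20% of the pretreatment mean (0.55 day/week"), at 80% power and a 5% significance level. The next step is the allowance for losses: "Allowing for a 20% drop-out rate, the aim for inclusion will be 240 children".

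Under Statistical analyses, a child with no weekly answer in any of the last four weeks is left out of the main analysis, which the article calls complete-case. Multiple imputation appears only as a sensitivity analysis. The same section puts the baseline level into the regression model for each change score.

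The abstract's Methods paragraph gives one size only: "There will be 100 children in each arm". It mentions neither 240 nor a drop-out allowance.

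**The concern.** A drop-out allowance exists so that the number left after losses is still the number the power calculation asks for. That requires dividing by the retained fraction. Adding 20% to the required number and then losing 20% of the larger total does not return to the starting point. The figure of 240 has the form of the first operation, so the target and the drop-out rate stated in the same sentence do not fit the 200 that precedes them.

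At stake is whether the trial can claim 80% power at its own inclusion target and under its own assumption about losses. In addition, a reader who sees only the abstract cannot tell whether its 100 per arm counts children included or children analysed.

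**Working it through.** **Inputs (Sample size considerations, unless noted)**
- Pre-treatment mean: 11 days per four weeks, or 2.75 per week.
- Target difference: 20% of that mean, i.e. 0.55 day per week, or 0.20 × 11 = 2.2 days per four weeks.
- SD of change: 5.58. The text labels it as weekly; its scale is settled in step 1.
- Power 80%, significance level 5%. Sidedness is not stated; two-sided is assumed.
- Allocation 1:1 (Randomization section).
- Drop-out 20%, inclusion target 240.

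**Step 1. Reproduce the plan's 100 per group.** The normal-approximation formula is n per group = 2 × (1.960 + 0.842)² × (SD / difference)².
- SD 5.58 on the four-week scale, difference 2.2: 2 × 7.849 × (2.536)² = 101.0. The t-test version gives 102. Both agree with the stated 100 to within rounding.
- SD 5.58 on the weekly scale, difference 0.55: about 1,616 per group. This does not match.
- One-sided 5% on the four-week scale: 80 per group. This does not match.

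So the stated figure is reproduced with a two-sided test and 5.58 read as a four-week SD (5.58 / 4 = 1.395 days per week). That scale is an inference from the arithmetic, and all power figures below depend on it.

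**Step 2. Reproduce the 240.** 200 × (1 + 0.20) = 240, the stated target.

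**Step 3. Apply the stated drop-out to it.**
- Retained: 240 × (1 − 0.20) = 192, or 96 per arm, which is 8 fewer than 200.
- Target that retains 200: 200 / (1 − 0.20) = 250.
- Largest drop-out at which 240 still retains 200: 1 − 200/240 = 16.7%.

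**Step 4. Power at the retained number.** Unadjusted two-sample t-test, two-sided 5%, standardised difference 2.2 / 5.58 = 0.394, noncentrality 0.394 × √(n/2):

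| Analysed per arm | Noncentrality | Power |
|---|---|---|
| 96 | 2.73 | 77.6% |
| 100 | 2.79 | 79.2% |
| 102 | 2.82 | 80.0% |

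The multiplication slip therefore costs 79.2 − 77.6 = 1.6 points. The other 0.8 point below 80% comes from rounding the required number to 100 and is a separate matter.

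**Step 5. What the baseline covariate could return.** Let r be the correlation between the change score and its baseline value. The article gives no r, so these values are assumptions. The residual SD is 5.58 × √(1 − r²). At 96 per arm, power is 79.2% for r = 0.20, 80.1% for r = 0.25, 81.3% for r = 0.30 and 84.3% for r = 0.40.

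**The case against.** Three objections deserve an answer.

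**The planned analysis is more precise than the calculation.** It adjusts for baseline, and step 5 shows that a correlation of about 0.25 would be enough to restore 80% at 96 per arm. This stands as a reason to expect little practical harm. It does not make the printed figures consistent: the sample size section does not invoke the adjustment and gives no correlation, and r could be smaller.

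**Drop-out need not mean loss from the analysis.** One weekly answer in the last four weeks is enough to be analysed, the text messages do not depend on clinic attendance, and reminders are sent automatically. The article does not define drop-out, so real losses from the analysis may well be below 20%. But if the 20% did not refer to children missing from the analysis, there would be no reason to raise the target for it.

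**The abstract may not conflict with the body.** Its 100 per arm equals the required number in the sample size section and can be read as the analysable number with the allowance left out. This stands. A reader might instead infer a rival inclusion target of 200, with 80 per arm left after 20% loss. The body of the article plans no such scenario, so the abstract calls for alignment only.

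A reader might also take "180 children were included and recruitment is expected to be concluded by June 2019" to mean that 240 will not be reached. The article gives one cumulative count and an expected closing month, but no recruitment rate. It describes approaches through schools and local media, which need not yield a steady flow. A projection would rest on an assumed constant rate, and the text does not support a power figure built on one.

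**Conclusion.** The point holds, as a minor arithmetic error. At the stated 20% drop-out, an inclusion target of 240 gives 192 analysable children and not 200; the target matching the stated rate is 250. Power at 96 per arm is 77.6%, which is 1.6 points below that at 100 per arm and 2.4 points below the stated 80%.

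The head counts follow from the article's own figures, provided that drop-out means absence from the complete-case analysis. The power figures rest on three further assumptions: 5.58 is a four-week SD, the test is two-sided, and there is no covariate adjustment. A reader might infer that the trial is seriously underpowered. The documents do not support that: the shortfall is four children per arm, and the planned adjustment could offset it.

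**What to change.** Change the sentence on the allowance in one of two ways:
- say that 240 included children with 20% drop-out give 192 analysable children (96 per arm) and about 78% power for 0.55 day per week, unadjusted; or
- say that 240 retains the required 200 only if drop-out is at most 16.7%.

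In the abstract, say that 100 per arm is the analysable number and that 240 is the inclusion target.

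The cost is wording only. Neither option requires more children or a change to the analysis; under the first, the stated power falls by about two points.

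When the sentence is edited, confirm that 5.58 refers to the four-week scale, since the quoted power depends on it.
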